## Background

Melanoma has become a growing interdisciplinary problem in public health worldwide. According to the World Health Organization, the incidence of melanoma is increasing faster than any other cancer in the world. Melanoma is the third most common cancer in Australia and the fifth in the USA. The American Cancer Society estimated that about 70,230 new melanomas were diagnosed in the USA during 2011 [1], resulting in about 8790 deaths [2]. However, melanoma accounts for < 5% of skin cancer cases, yet it causes > 75% of skin cancer deaths and thus poses a significant health issue and economic burden [3].

Because melanoma, depending on tumor depth, metastasizes early into regional lymph nodes [4, 5], sentinel lymph node excision (SLNE) is probably the most important diagnostic and potentially therapeutic procedure for melanoma patients [6, 7]. Recommendations for the use of SLNE for primary melanoma are therefore included in the current American Joint Committee of Cancer guidelines. Critics argue that the routinely performed SLNE is a cost-intensive surgical intervention with potential morbidity that does not offer patients any advantage in overall survival [8–11]. Moreover, the SLNE of melanoma has a very high false-negative rate of up to 44% [12, 13]. The current gold standard for detection and targeted extirpation of the sentinel lymph node (SLN) is preoperative lymphoscintigraphy. Single-photon emission computed tomography (SPECT)/CT provides complementary functional and anatomical information and has been shown to be superior to planar imaging in a number of indications [14]. The advantages include more accurate anatomical localization, identification of false positives (due to contamination or spillover from the injection site), reduction in the number of false negatives (visualization of nodes not seen on planar imaging), and alteration of the surgical approach. We thus believe that sentinel lymph node SPECT/CT can provide valuable information before SLN biopsy and advocate its use in a range of tumors such as truncal and head and neck melanomas. Due to the lack of prospective multicenter randomized trials, many clinicians are uncertain in regard to preoperative SPECT/CT imaging for SLNE in melanoma patients, especially regarding distant metastasis-free survival, overall survival, and costs.

Clinical experience and small non-randomized clinical trials reported on the advantage of preoperative imaging with SPECT/CT [15, 16].

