#### Inclusion criteria

Patients may be included in the study only if they meet all the following criteria:patients with malignant melanoma in American Joint Committee of Cancer stages Ib / II;tumor depth of ≥ 1.0 mm;age 18–75 years;have a primary melanoma that is cutaneous (including head, neck, trunk, extremity, scalp, palm, sole, subungual skin tissues);Eastern Cooperative Oncology Group (ECOG) performance status 0–1;life expectancy of at least five years from the time of diagnosis, not considering the melanoma in question, as determined by the principal investigator;willing to return to the trial center for follow-up examinations and procedures as outlined in the protocol;randomization must be completed no more than 120 days following the diagnostic biopsy of the primary melanoma;negative pregnancy test for female and effective contraception for both male and female participants if the risk of conception exists;signed written informed consent before the performance of any trial-specific procedure.

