### Statistical methods

The primary analysis of efficacy and superiority of SPECT/CT-aided SLNE versus standard SLNE regarding distant metastasis-free survival will be tested confirmatorily on the intent-to-treat analysis set with a significance level of 5% by a two-sided test [21] of the regression coefficient for the treatment variable from a Cox proportional hazards model [22, 23]. This test coincides with the log-rank test. It is more suitable than the weighted relatives of the log-rank test because treatment achievements are expected to be observed at later points in time. The analysis with the Cox model will adjust for the factors of the randomization, that is site, sex, tumor depth (< 4.0 mm or ≥ 4.0 mm) and tumor location (head and neck region, yes or no). Due to the nature of the primary outcome variable, there will not be any missing data for it. No imputation of missing data has to be performed for the primary analysis. First, the realization of a time-to-event variable as distant metastasis-free survival is either an event or a censored observation, and thus, never missing. Second, missing values for the independent variables in the Cox proportional hazards model are neither possible as these variables are the factors of the randomization and the randomization cannot take place with one or more of its factors being missing.

Results will be displayed as adjusted Kaplan–Meier curves and reported as adjusted hazard ratios (HR) from the Cox proportional hazards model with corresponding 95% confidence intervals (CI). Sensitivity analysis for the primary endpoint will be performed using Kaplan–Meier curves and HRs not adjusting for the factors of the stratified randomization. Furthermore, a per-protocol analysis, adjusted and unadjusted for the stratification variables, will be conducted. Another sensitivity analysis will account for the fact that study patients may withdraw from this trial between randomization and SLNE as they may not be satisfied with the study group they were assigned to. Thus, we will create a worst case scenario treating all study patients who withdraw from the trial between randomization and SLNE as if they had the primary outcome event at randomization. Adjusted and unadjusted analyses will be repeated under this worst case scenario.

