### Sample size

Sample size calculations have been carried out with PASS 13 Power Analysis and Sample Size Software [PASS 13, 2014] using the formula of Schoenfeld [26]. In a non-randomized clinical trial at the university hospital Essen with 402 melanoma patients, we observed a five-year distant metastasis-free survival cumulative survival probability of 67% determined using the Kaplan–Meier product limit estimator for patients after standard SLNE (n = 254, 46% with T2 and 31% with T3) which is in line with Morton et al. [27]. In the SNEPS trial, we intend to include patients of stages I and II but with an expected classification of mainly stage II or III after postoperative histology. We therefore assume to observe a comparable treatment effect in the control group. For patients with SPECT/CT-aided SLNE (*n* = 148), we observed a five-year distant metastasis-free survival cumulative survival probability of 77% in the non-randomized clinical trial. This corresponds to a HR of 1.56 (95% CI 1.06–2.30). This HR seems relatively large at first sight, but given the high distant metastasis-free survival rates it is equivalent to a difference in five-year distant metastasis-free survival of 10%, which is rather small for such a late time point, but still clinically relevant and in the range of generally accepted effect sizes in oncology trials.

The sample size calculation is based on the intention to compare the distant metastasis-free survival times in both groups with the partial likelihood method of Cox [21] that tests whether the regression coefficient from a Cox proportional hazards model [28] is equal to zero and that coincides with the log-rank test [24]. Given the two-sided version of this test with a significance level of 5% and assuming a true HR of 1.56, 214 events have to be observed in total to achieve a power of 90%, 126 in the control group, and 88 in the experimental group. These results assume that the HR is constant throughout the study. For the anticipated proportion of patients having a distant metastasis during the study, we assume 33% in the control group and 23% in the SPECT/CT-aided group. Thus, 380 evaluable patients per group (760 in total) have to be recruited. To account for 10% dropouts or loss of information because of non-compliance to follow-up visits, a total of 836 patients will be randomized.

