### Methods against bias

After initiation of the sites, all patients will be consecutively screened and all eligible patients willing to participate will be included in the trial. In order to achieve comparable groups regarding possibly relevant predictors and achieve balanced group sizes per site, patients will be allocated in a concealed manner by central web-based preoperative 1:1 stratified (minimization algorithm [Pocock and Simon] with biased coin principle) randomization with stratification factors site, sex, tumor depth (< 4.0 mm or ≥ 4.0 mm), and tumor location (head and neck region, yes or no). The primary analysis will control for the factors of the randomization. Each patient who is registered will be randomized and each randomized patient is part of the intent-to-treat analysis. It is not feasible to blind the patient or initial reader of the SPECT; however, physicians responsible for the follow-up and detection of distant met\astases will be blinded against the SPECT status by non-accessibility of the SPECT electronic case report form. In addition, the local interdisciplinary tumor board and an independent endpoint committee will review written reports of potential outcomes. The surgical technique will be identical in all participating sites and only operating physicians with a cumulative experience > 100 SLN surgical procedures will participate. The impact of a learning curve is thereby small. Performance bias will be avoided to a certain extent by certifying only experienced surgeons. All participating sites in Germany are certified by OncoZert and have a quality management system. All clinical investigators involved in this trial are experienced in performing SLN surgery, using preoperative SPECT/CT imaging and are trained in Good Clinical Practice. This allows for reduction of interrater variability to a minimum.

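### The primary Cox model uses tumour depth only as a split at 4.0 mm; adding log depth in mm would give a small, nearly free gain in precision

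*Protocol article*

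**What the plan says.** Under Statistical methods, the primary Cox model "will adjust for the factors of the randomization, that is site, sex, tumor depth" (below versus at or above 4.0 mm) and for head and neck location. Methods against bias lists the same variables with the same cut for the minimization: "stratification factors site, sex, tumor depth (< 4.0 mm or ≥ 4.0 mm), and tumor location (head and neck region, yes or no"), and says that the primary analysis will control for them.

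The sensitivity analyses named for the primary endpoint are an unadjusted analysis, per-protocol analyses with and without adjustment, and a worst case for withdrawals between randomization and surgery. None uses depth more finely.

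Three other places bear on the point:
- Inclusion criteria require a "tumor depth of ≥ 1.0 mm".
- The Background says: "Because melanoma, depending on tumor depth, metastasizes early into regional lymph nodes".
- Sample size describes the historical standard-SLNE cohort (n = 254) as "46% with T2 and 31% with T3".

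**The concern.** Depth is the one tumour characteristic on which the article says early spread to the regional nodes depends. It has to be assessed in every patient, once against 1.0 mm for entry and once against 4.0 mm for allocation. Both the minimization and the model then reduce it to two levels. Within the lower level, a tumour just over 1 mm and one just under 4 mm count as the same. Depth differences between the arms inside that level are neither balanced by design nor adjusted for.

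At stake are a modest amount of precision in the primary estimate, and an answer to the question that readers of an open-label trial will ask: did the arms happen to differ in depth? The model is stated explicitly in the article, so this is not a detail left to an analysis plan that is not shown.

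**Working it through.** **The plan's own figure.** For HR 1.56, two-sided 5% and 90% power, the Schoenfeld formula gives 4 × (1.960 + 1.282)² / (ln 1.56)² = 42.03 / 0.1978 = 212.5, so 213 events. The plan states "214 events have to be observed in total to achieve a power of 90%, 126 in the control group, and 88 in the experimental group". By arm, 380 × 0.33 = 125.4 and 380 × 0.23 = 87.4, which round up to 126 and 88. With 214 events the power is 90.2%. The figure reproduces, and it takes no credit for covariate adjustment.

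**Share of patients in one level.** 46% + 31% = 77% of the historical standard-SLNE cohort. The article gives no mm limits for T2 and T3. If both are assumed to lie at or below 4.0 mm, the lower level holds at least 77%, and up to 100% if the undescribed 23% were thinner than T2. Carried over to this trial, 77% is 585 of 760 evaluable patients.

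**Effect of the coding on power.** The documents give no hazard ratio for depth, so a range is assumed. Cox simulation, 4000 runs per row:
- N = 760, balanced 1:1 within depth stratum;
- treatment HR 1.56, 33% control events at five years;
- T2/T3/T4 = 46/31/23% (T4 share assumed), at 1–2, 2–4 and 4–8 mm, uniform within category;
- no site effect.

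| Assumed HR per doubling of depth | No depth term | Two levels (planned) | Continuous log depth instead |
|---|---|---|---|
| 1.3 | 0.881 | 0.882 | 0.882 |
| 1.5 | 0.884 | 0.891 | 0.897 |
| 2.0 | 0.864 | 0.886 | 0.895 |
| 2.5 | 0.846 | 0.890 | 0.905 |

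The estimated HR is 1.54 to 1.56 with two levels and about 1.56 with continuous depth.

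**Adding log depth to the two-level factor.** A separate simulation (3000 runs per scenario, N = 760, about 213 events, same assumed T mix) gave these gains in information, that is, in the squared ratio of the test statistics:

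| HR per doubling | 1.3 | 1.5 | 1.8 | 2.0 | 2.5 |
|---|---|---|---|---|---|
| More information | 0.6% | 1.6% | 2.2% | 2.8% | 6.4% |

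In events, 214 × 0.006 = 1.3 and 214 × 0.064 = 13.7. Simulated power rose by 0.2 to 1.9 points, and by 0.4 to 1.2 points when risk was made to flatten above 4 mm. As a check on the top of the range, √(214 × 1.064) × 0.4447/2 − 1.960 = 1.395, which is 91.9% power against 90.2%, a gain of 1.7 points.

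**Chance imbalance inside the lower level.** With the same assumed limits:
1. Variance of log2 depth = 0.0814 within a category + (46/77)(31/77) × 1² = 0.2405 between categories, total 0.322. SD = 0.567.
2. Standard error of the arm difference with 585 patients = 0.567 × √(4/585) = 0.0469. Two SD = 0.0938 doublings.
3. Shift in the overall HR ≈ exp(ln g × 0.0938 × 0.77), where g is the HR per doubling. This is 1.019 at g = 1.3, 1.030 at 1.5, 1.051 at 2.0 and 1.068 at 2.5.

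So an imbalance of that size moves the HR by about 2% to 7%. At g = 2.0, a true 1.56 would appear as 1.56/1.051 = 1.48 or 1.56 × 1.051 = 1.64. Step 3 weights by patients. Weighting by the lower level's share of events, which is smaller when depth is strongly prognostic, would reduce the larger figures.

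**The case against.** The strongest reply is that nothing here is wrong. The model adjusts for the factors exactly as they were used in the allocation, the two sections agree, the practice is accepted and the test keeps its size. All of that stands.

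A reader might infer that depth imbalance below 4.0 mm biases the primary result. The documents do not support this. Randomization balances depth in expectation, and the confidence interval already allows for chance imbalance in a covariate left out. Adjustment narrows that uncertainty; it does not remove a systematic error.

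A reader might also take three quarters of patients in one level as a fact about this trial. It is an extrapolation from a historical cohort with assumed T limits. Nor does the article call depth the driver of distant metastasis: its remark concerns early spread to regional nodes, and the primary endpoint is distant metastasis-free survival.

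The gain is small, and the two-level factor already secures much of it. At 2.5-fold risk per doubling, power goes from 0.846 without depth to 0.890 with the split and 0.905 with continuous depth. The simulations also favour log depth, because the fitted form matches the assumed one. The gain shrinks but survives when risk flattens above 4 mm.

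The last objection has practical force. The article argues that model covariates cannot be missing because they are randomization factors. Exact depth in mm is not one of them, and the article does not say that it is recorded for every patient. This is a condition to check, and it does not count against the change.

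**Conclusion.** The point holds as a minor improvement. The planned analysis is valid and consistent with the randomization, and the sample size does not depend on how depth is coded. What is given up is about 0.6% to 6% of information, equivalent to about 1 to 14 of 214 events and 0 to 2 points of power, together with protection against a chance shift in the HR of about 2% to 7% at two standard deviations.

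These sizes rest on assumptions that the documents do not supply: the risk gradient per doubling of depth, the mm limits of T2 and T3, the share and depth range of T4, and a case mix like that of the historical cohort. With a shallow gradient the gain is close to nil. The figures do not support calling the trial underpowered or its primary estimate biased on account of this coding.

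**What to change.** Before data are analysed, prespecify log tumour depth in mm as an additional covariate in the primary Cox model. Keep all randomization factors, including the split at 4.0 mm, and retain the dichotomy-only model as a sensitivity analysis.

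The cost is a short addition to the analysis plan and no additional patients. Two things must be settled with it. Confirm that the exact depth, and not only its class, is recorded for every patient. State a simple rule for any missing value, because the article's argument that covariates cannot be missing covers only the randomization factors.

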### Blinding

Not applicable as this is an open-label study.

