Because treatment achievements are expected to be observed relatively late in time, no interim analysis will be performed. Subgroup analyses will be carried out in the levels of the randomization factors.

Standard safety analyses will be done for all serious adverse events (SAEs) reported and documented during the trial period. Additionally, SAEs from the five most common system organ classes of the Medical Dictionary for Regulatory Activities (MedDRA®) will be pooled by system organ classes and analyzed as time to SAEs occurrence with the Anderson–Gill model [22] that can account for recurring events with cause-specific hazards in the case of competing risks. Furthermore, as recommended recently [24], the mean frequency function [25] will be used to allow the comparison in terms of absolute event probabilities.

All secondary analyses will be done exploratively, i.e. without adjustment for multiplicity. Standard statistics appropriate for the given level of measurement of the respective outcome will be applied and for evaluating the diagnostic performance of SPECT/CT aided SLNE (e.g. sensitivity, false-negative rate). For secondary analyses, imputation of time-to-event variables or factors used in the Cox proportional hazards model is not necessary due to the same reasons as for the primary analysis. For the remaining endpoints, where missing data are possible, multiple imputation methods are used with all factors of the randomization being included in the imputation model. In the sensitivity analysis, missing outcome data are replaced using a worst case scenario.

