## Discussion

In this multi-center, unblinded superiority clinical trial SPECT/CT-aided SLNE versus standard SLNE in melanoma patients will be compared. The primary efficacy endpoint is distant metastasis-free survival. Secondary endpoints comprise overall survival, disease-free survival, rate of local relapses within the follow-up period (false-negative rate of SLN), number of positive SLN (sensitivity, false-positive rate), complication rate, quality of life, quality-adjusted life years, inpatient days, and overall costs during hospital stays.

Because melanoma, depending on tumor depth, metastasizes early into regional lymph nodes [4], SLNE is probably the most important diagnostic and potentially therapeutic procedure for melanoma patients. Recommendations for the use of SLNE for primary melanoma are therefore included in the current American Joint Committee of Cancer guidelines.

All study patients will at least receive the gold standard (lymphoscintigraphy). However, this procedure has resulted in some controversies in international discussions [29, 30]. Therefore, two diagnostic modalities will be compared. In the experimental study, one group of patients will additionally receive SPECT/CT. No additional risk is expected. From the experts of the German Association for Radiology, the radiologic diagnostic procedures in this study are evaluated as being according to medical standard so that no approval from the federal authority for radiation protection is required. Central ethical approval has been confirmed from Institutional Review Board of the University Hospital Essen (ref. approval no. 18–8288-BO) and we will not begin recruiting at other centers in the trial until local ethical approval has been obtained.

All investigators and the involved contract research organization (Alcedis GmbH, Gießen) ensure that the requirements of the World Medical Association Declaration of Helsinki are met and that the conduct of the trial is in accordance with current ICH guidelines for good clinical practice.

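### The worst-case sensitivity analysis codes pre-SLNE withdrawals as events in both arms, so it is not the worst case for a superiority claim and can favour SPECT/CT if more control patients leave

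*Protocol article*

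**What the plan says.** The Statistical methods section of the protocol article makes an adjusted Cox model on the intent-to-treat set the confirmatory analysis of distant metastasis-free survival. It then lists sensitivity analyses: unadjusted, per-protocol, and one for patients who leave between randomization and SLNE, "as they may not be satisfied with the study group they were assigned to". That last analysis works by "treating all study patients who withdraw from the trial between randomization and SLNE as if they had the primary outcome event at randomization". No arm is singled out. The section continues: "Adjusted and unadjusted analyses will be repeated under this worst case scenario".

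Three other statements bear on who might leave. On blinding, the article says "Not applicable as this is an open-label study". The Discussion says "All study patients will at least receive the gold standard (lymphoscintigraphy"), that "one group of patients will additionally receive SPECT/CT", and "No additional risk is expected". The article gives no pre-SLNE withdrawal rate, overall or by arm.

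**The concern.** A worst case for a superiority claim should be the coding of unknown outcomes that hurts the claim most. Here that means failures among SPECT/CT leavers and no failures among control leavers. The planned rule imputes failures to control leavers too, and each of these counts for SPECT/CT.

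The stated reason for the analysis is that withdrawal may depend on the allocation. If it does, and controls leave more often, the rule adds more time-zero events to control than to SPECT/CT. The analysis would then strengthen the claim in the very situation that it is meant to guard against. A positive result labelled worst case would be read as robustness, although part of it came from differential withdrawal. No other listed sensitivity analysis targets allocation-driven withdrawal among all randomized patients.

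**Working it through.** **Inputs from the article.** 836 randomized 1:1, so 418 per arm; two-sided 5% test; 33% of controls with an event (five-year survival 67%); design HR 1.56 and 214 events for 90% power. HRs here are control versus SPECT/CT, as in the article, so values above 1 favour SPECT/CT.

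**The plan's own figure.** Schoenfeld: 4 × (1.960 + 1.282)² / (ln 1.56)² = 212.5, so 213 events against 214 stated. It reproduces.

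**Assumptions.** Pre-SLNE withdrawal rates by arm are not given, so a range is used. Times are exponential, with follow-up of five years unless stated.

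**Step 1: logic.** Take any control patient who withdraws before SLNE. Changing that patient from an event at randomization to event-free at the cut-off removes a control event and moves the estimate away from SPECT/CT. A more adverse scenario therefore exists whenever at least one control patient withdraws.

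**Step 2: hand check with no true effect.** Let c and s be the withdrawals in control and SPECT/CT, all coded as events at time zero. With equal arms, the log-rank excess of control events at time zero is c − (c + s)/2. Total events are D = (c + s) + 0.33 × (836 − c − s), and the standard deviation of the log-rank numerator is about √(D/4). The shift in z is the excess divided by that value, and the chance of significance for SPECT/CT is about P(Z > 1.96 − shift).

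- 3%/1% (13 and 4): excess 4.5; D = 17 + 270.3 = 287.3; SD 8.47; shift 0.53; chance 7.7%.
- 5%/1% (21 and 4): excess 8.5; D = 25 + 267.6 = 292.6; SD 8.55; shift 0.99; chance 17%.
- 8%/2% (33 and 8): excess 12.5; D = 41 + 262.4 = 303.4; SD 8.71; shift 1.44; chance 30%.
- 5%/5% (21 and 21): excess 0; shift 0; chance 2.5%.
- 1%/5% (4 and 21): excess −8.5; shift −0.99; chance 0.2%.

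**Step 3: simulation of the planned rule, no true effect** (418 per arm, unadjusted log-rank or Cox test, 400 to 3,000 trials per setting):

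| Withdrawal, control/SPECT-CT | Significant for SPECT/CT |
|---|---|
| 2%/1% | 3.6% |
| 3%/2% | 4.5% |
| 3%/1% | 7% |
| 5%/2% | 12% |
| 5%/1% | 16% |
| 8%/2% | 32% |
| 3%/3% and 5%/5% | about 2% |
| 2%/3% | 0.8% |
| 1%/5% | 0.3% |

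The simulation agrees with the hand check. With three years of follow-up, the stated minimum, there are fewer real events and the effect is larger: 22% at 5%/1% and 41% at 8%/2%.

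**Step 4: planned rule against an adverse rule** (events at randomization for SPECT/CT withdrawals only, control withdrawals event-free to five years), true HR 1.56. HRs simulated as SPECT/CT versus control are inverted, for example 1/0.600 = 1.67.

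| Withdrawal, control/SPECT-CT | Planned rule HR | Adverse rule HR |
|---|---|---|
| 3%/1% | 1.64 | 1.44 |
| 5%/2% | 1.67 | 1.36 |
| 8%/2% | 1.79 | 1.30 |
| 2%/2% | 1.51 | 1.40 |
| 5%/5% | 1.44 | 1.18 |
| 2%/5% | 1.34 | 1.24 |
| 2%/8% | 1.19 | 1.10 |

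The adverse rule is harsher on SPECT/CT in every row. In the control-heavy rows the planned rule exceeds the true 1.56.

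**Step 5: effect on power.** At 5%/1% and a true HR of 1.3, power is 53% with withdrawals censored and 85% to 86% under the planned rule. At the design HR of 1.56 it moves from 91% to 99%.

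**The case against.** The strongest reply is that the direction is assumed. The article says only that patients may be dissatisfied and names no arm. Every control patient receives what the article calls the gold standard, while SPECT/CT adds a procedure and a radiation dose, described as below 3 mSv. With equal or SPECT/CT-heavy withdrawal the planned rule dilutes the effect or works against SPECT/CT: at a true HR of 1.3, where censoring gives about 51% to 54% power, it gives 44% at 5%/5% and 13% at 1%/5%. This stands. A reader might infer that the plan expects control patients to leave, or that the rule always favours SPECT/CT; the documents support neither.

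A second reply is that this is one sensitivity analysis among several and cannot change the formal result. This also stands. A reader might infer that the trial's type I error is inflated. It is not, because the confirmatory test does not use this rule. At the design effect the conclusion would hardly change either.

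A third reply is that giving every leaver the worst outcome is a legitimate composite-type rule. That is fair as a description, but it supports a change of name: a composite of withdrawal or metastasis is not a worst case for the comparison.

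It is also tempting to extend the point to the secondary endpoints, where "missing outcome data are replaced using a worst case scenario". That sentence gives no direction by arm, and a condensed article may leave this to the full protocol or SAP, so it is not evidence of the same error. Nor does the article's silence on follow-up after withdrawal show that such follow-up is not planned.

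**Conclusion.** The point holds, with moderate severity. That the rule is not the worst case rests on logic alone and needs no assumed rate beyond one control withdrawal. That it can favour SPECT/CT is conditional on more controls than SPECT/CT patients leaving before SLNE. The open-label add-on design makes this plausible, but no document states it.

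The size depends on the assumed imbalance: a mild one (2%/1% or 3%/2%) raises false significance for SPECT/CT only to about 4% or 5%, and the large figures need a strongly control-heavy pattern. The simulations use unadjusted tests and exponential times, and runs at the same setting differed by a few percentage points (15% to 18% at 5%/1%). What is at risk is false reassurance about robustness, mainly when the true effect is nil or smaller than planned.

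**What to change.** Define the worst case against the claim: pre-SLNE withdrawals count as events at randomization in the SPECT/CT arm only, and control withdrawals stay event-free to the cut-off. Add a tipping-point analysis by arm that spans the range between this rule and the present one. Report the number of pre-SLNE withdrawals by arm beside these results. Keep the both-arms rule if wanted, but relabel it as a composite analysis. The changes should be fixed before withdrawals by arm are known.

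The cost is a few lines of analysis-plan wording, one more programmed scenario and the tipping-point runs. Sample size and trial conduct do not change. The sensitivity result may look less favourable: with no true effect the adverse rule gave significance for SPECT/CT in 0.5% of trials or fewer at 3%/1%, 5%/2% and 8%/2%, and at the design HR its power in those settings was 79%, 62% and 49%. It should therefore be presented as a deliberate bound, with the tipping-point analysis showing how far towards it the data would have to go.

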### Randomization

Patients with malignant melanoma are allocated by 1:1 randomization to be treated with SLNE with or without preoperative hybrid SPECT/CT.

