### Treatment plan

The visit scheme of the SNEPS trial is depicted in Fig. 4. Lymphoscintigraphy (and SPECT/CT in Arm A) for evaluation of sentinel nodes in combination with surgical intervention can be performed in one day or over two days. In case of a two-day protocol, the radiation of the radioactive substance injected on day 1 is sufficient for surgery on day 2.

Therefore, one or two treatment visits (imaging and surgical intervention) are planned per patient. Patients will be followed up for a minimum of 36 months (follow-up visits and examinations to be performed every three months are specified).

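### The mean frequency function of recurring SAEs is said to give absolute event probabilities, but it gives the mean number of SAEs per patient

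*Protocol article*

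**What the plan says.** The safety paragraph under Statistical methods has three layers.

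- General: "Standard safety analyses will be done for all serious adverse events (SAEs) reported and documented during the trial period". The content of these analyses is not spelled out.
- Supplementary: SAEs from the five most common MedDRA system organ classes "will be pooled by system organ classes and analyzed as time to SAEs occurrence", using an Andersen-Gill model "that can account for recurring events with cause-specific hazards in the case of competing risks".
- Absolute scale: to complement the hazard-based model, "the mean frequency function [25] will be used to allow the comparison in terms of absolute event probabilities".

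Nothing in the article redefines the mean frequency function as a first-event quantity. For context, Treatment plan says "Patients will be followed up for a minimum of 36 months", and Sample size says "a total of 836 patients will be randomized".

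**The concern.** The paragraph chooses a recurrent-event model and then attaches the word probability to the summary that goes with it. A recurrent-event mean counts every SAE: a patient with three SAEs in a class contributes three. A probability of an SAE counts each patient at most once. The two answer different questions, namely how many SAEs occur per patient and what share of patients have any.

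At stake is the meaning of the absolute safety comparison between SPECT/CT-aided and standard sentinel node excision. An analyst who takes the sentence literally would report mean counts as risks. The risk in each arm would then look too high wherever patients have repeated SAEs. A few patients with many SAEs in one arm could also be read as more patients being harmed in that arm.

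**Working it through.** **Inputs from the article.** Events are recurring, with competing risks, and are pooled within organ class. Follow-up is at least 36 months, so second SAEs in a class are possible. Allocation is 1:1 of 836 patients, so 836/2 = 418 per arm. The article gives no SAE rate and no recurrence rate, so it has no figure to reproduce. Every rate below is an assumption.

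**Step 1: the identity.** Let N(t) be a patient's number of SAEs in a class by time t, with no further SAEs after death. Then

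mean frequency function = E[N(t)] = P(N(t) ≥ 1) + P(N(t) ≥ 2) + P(N(t) ≥ 3) + …

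The first term is the probability of at least one SAE. The remaining terms are zero only if nobody has a second SAE by t. So the function is never below the probability, and it has no upper bound of 1. Example: three patients with 0, 1 and 3 SAEs give a mean of 4/3 = 1.33, while the proportion affected is 2/3 = 0.67.

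**Step 2: size of the overstatement.** Write M for the mean number of SAEs per patient in a class and P for the probability of at least one. Ignoring death,

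- Poisson counts: P = 1 − exp(−M)
- Gamma frailty with variance θ: P = 1 − (1 + θM)^(−1/θ)

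The overstatement is M/P.

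| Assumed M | P, Poisson | P, θ = 2 | M/P |
|---|---|---|---|
| 0.05 | 0.0488 | 0.0465 | 1.02 to 1.08 |
| 0.1 | 0.0952 | 0.0871 | 1.05 to 1.15 |
| 0.3 | 0.2592 | 0.2094 | 1.16 to 1.43 |

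At M = 0.05, even with θ = 4, P is 0.0446, so the gap is 0.05 − 0.0446 = 0.0054, about half a percentage point.

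**Step 3: the comparison of arms.** Suppose the same share of patients is affected in both arms and only recurrence differs. The mean is the share affected times the SAEs per affected patient.

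- 10% affected, 1.2 versus 1.5 SAEs each: 0.10 × 1.2 = 0.12 and 0.10 × 1.5 = 0.15. The difference in means is 0.03; the difference in risk is 0.
- 20% affected, 1.2 versus 1.8 SAEs each: 0.20 × 1.2 = 0.24 and 0.20 × 1.8 = 0.36. The difference in means is 0.12; the difference in risk is 0.

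In a simulation of the first case (418 per arm, 4000 runs, complete follow-up, two-sided 5% z-test), the test on mean counts rejected in about 16% of runs and the test on the proportion affected in about 5.6%. The 16% is power to detect a true difference in mean counts. It would be an error only if the result were reported as a difference in risk.

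**The case against.** The strongest defence is that only the label is at fault. The mean frequency function suits recurring SAEs with competing risks. The sentence can be read loosely as promising an absolute scale next to the hazard ratios, and the article does not say that the values will be tabulated as the share of patients with an SAE. This stands in part: the estimator should stay. But the sentence names what is to be compared, and what it names is not what the function estimates.

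Second, a reader might infer that the trial will have no patient-level SAE risk at all. The article does not support that. The organ-class analyses are additional to standard safety analyses, whose detail a condensed article may leave to the full protocol or analysis plan, and these may well include the proportion of patients with an SAE. Complication rate is also a separate secondary endpoint. None of this corrects the label on the organ-class analysis.

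Third, a reader might infer that the reported risks will be materially inflated and that an arm difference would be spurious. Neither is shown. With no SAE rate given, materiality cannot be judged, and at low per-class means the gap is small. The article describes one or two treatment visits and expects no additional risk from SPECT/CT, so it offers no support for high per-class rates or for recurrence that differs by arm. A difference in mean counts is also a genuine difference in SAE burden; it misleads only when read as a difference in the share of patients affected.

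**Conclusion.** The sentence states a wrong property of a named analysis. The mean frequency function of recurring SAEs is an expected count per patient. It coincides with an absolute event probability only when no patient has a second SAE in the class, and the choice of a recurrent-event model means that the plan does not assume this. The error follows from the definition and needs no assumption about rates.

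Its numerical size does rest on assumptions: the per-class mean, Poisson to gamma-frailty (variance 2) counts, and no allowance for death. The Working table gives the resulting range, which runs from slight at low means to considerable at 0.3.

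The reach is limited. This is a supplementary safety summary. The confirmatory test on distant metastasis-free survival, its significance level and the sample size are untouched. The correction is worth making because it is nearly free and settles what the absolute safety comparison means.

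**What to change.** Replace the sentence with wording to this effect: *The mean frequency function will be used to compare the arms in the mean number of SAEs per patient by time t. Absolute event probabilities will be compared with the Aalen-Johansen cumulative incidence of the first SAE in each organ class, with death as a competing event.*

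Keep the Andersen-Gill analysis and the mean frequency function as planned. Relabelling alone removes the misstatement; the first-event cumulative incidence delivers the probability comparison that the sentence sets out to make. If the full protocol or analysis plan already specifies such an estimate, a cross-reference is enough.

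The cost is one sentence and one standard estimate from SAE and death dates already collected. No patients, visits or procedures are added.
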